# Community-based intervention for prevention and management of chronic obstructive pulmonary disease in Nepal (COBIN-P trial): study protocol for a cluster-randomized controlled trial

**DOI:** 10.1186/s13063-021-05447-7

**Published:** 2021-07-21

**Keywords:** COPD, Community health workers, Nepal, Female Community Health Volunteers, Cluster randomized controlled trial

## Abstract

**Background:**

Chronic obstructive pulmonary disease (COPD) is one of the leading causes of death worldwide and the commonest of non-communicable diseases (NCDs) in Nepal. Risk factors like indoor and outdoor air pollution, a high prevalence of smoking, and the lack of awareness of COPD make it a serious public health concern. However, no attempt has been made in Nepal to estimate its burden and address the disease at the community level.

**Method:**

This study aims to evaluate the effect of a community-based health educational intervention administered by Female Community Health Volunteers (FCHVs) on the prevention and management of COPD. An open-label, two-group, community-based, cluster-randomized controlled trial will be implemented in the semi-urban area of Pokhara Metropolitan city (former Lekhnath Municipality) located in the Kaski district of Nepal. The estimated sample size of the intervention will be 1143. The unit of randomization is the ward (administrative unit) of the study area. The follow-up survey will be conducted immediately after 12 months of FCHVs-led interventions. The difference in the rate of decline of forced expiratory volume in 1 s (FEV_1_) and FEV_1_/FVC (forced vital capacity) ratio are the primary outcomes and the change in the proportion of modifiable risk factors of COPD, health-related quality of life scores, and change in knowledge of COPD will be secondary outcomes.

**Discussion:**

This study will estimate the burden of COPD, the magnitude of risk factors and generate evidence to mobilize community health workers for COPD prevention and management at the community level in Nepal.

**Trial registration:**

ClinicalTrials.gov NCT03797768. Registered on January 9, 2019.

## Background

Globally, non-communicable diseases (NCDs) are the leading causes of morbidity and mortality, accounting for the deaths of 41 million people annually [1]. Nearly three-quarters of NCDs-related global deaths occur in low- and middle-income countries (LMICs), like Nepal [2].

As of 2017, the Global Burden of Disease (GBD) study estimated that about 3.9 million people worldwide died of COPD, which is 5.7% of all deaths [1]. Far earlier than the World Health Organization (WHO) projection COPD to be the third most important cause of death worldwide by 2030 [3], the current estimation of the GBD study 2017 ranks it as the second killer disease globally [1].

The Global Initiative for Chronic Obstructive Lung Disease (GOLD) defines COPD as “a common, preventable and treatable disease that is characterized by persistent respiratory symptoms and airflow limitation due to airway and/or alveolar abnormalities usually caused by significant exposure to noxious particles or gases” [4]. COPD results from the interaction between genetic and environmental factors, including exposure to tobacco smoke, indoor and outdoor air pollution, and exposure to organic and inorganic dust, fumes, and gases [5].

WHO reports that 90% of COPD accounted for deaths occurs in LMICs [6]. Furthermore, COPD-associated mortality is predicted to increase by 160% in the Southeast Asian region in the coming decades [7]. COPD is one of the commonest forms of NCDs among the Nepalese adult population contributing to more than 40% of NCD cases among out-patients [8]. Such a high burden of COPD in the country has been attributed to the widespread use of traditional cooking stoves, mainly in the rural areas, and the burning of solid biomass fuels like animal dung, crop residue, and wood [9]. The national census of 2011 estimated that 75% of Nepalese populations use biomass fuels in poorly ventilated housing conditions [10]. Likewise, 27% of Nepali men (15–64 years) smoke tobacco while women (15–64 years) are also known to smoke (10%) considerably higher by Southeast Asian average [11]. The WHO STEPS survey in 2019 estimated that more than 33% of the Nepalese adult population (15–64 years) is exposed to second-hand smoking at home [12]. Similarly, a recent study in eastern Nepal revealed that the level of inadequate health literacy was 77% among patients with COPD [13].

These statistics suggest that addressing smoking along with indoor and outdoor air pollution remains the cornerstone of COPD prevention in Nepal. However, the COPD diagnosis with spirometry, its treatment, and management is usually limited to specialized tertiary level health facilities. It is beyond the reach of district health facilities in resource-limited countries [14]. On the other hand, more simple measures like spreading awareness on recognizing cough, sputum production, and breathlessness as essential symptoms have the potential to go a long way as a necessary aspect of public health care of COPD [15].

Most community-based programs studied previously focused particularly on pulmonary rehabilitation, smoking cessation counseling, improving health-related quality of life, self-management counseling, reducing hospital admissions, delivered mainly by physicians, nurses, and physiotherapists [16–22]. The FRESH Air project study in Uganda involved midwives, but the intervention included the delivering of health education messages on the dangers of biomass smoke to pregnant women and post-natal mothers through the regular ante- and post-natal clinics [23]. A published protocol intended to involve community health workers (CHWs) for supporting in the self-management of COPD cases in Bhaktapur district of central Nepal [24]. Likewise, a study reported that CHWs were invited for inputs during consultative meetings while designing probable self-management interventions in multimorbid COPD cases in rural Nepal [25]. However, none of the studies exclusively involved CHWs in COPD prevention and management for a healthy population, the population at risk, and COPD patients in Nepal. In the resource-constrained setting of Nepal, with a very low number of specialized health professionals in lung health, the involvement of CHWs remains a possible opportunity to curb the rising burden of COPD [26]. More than 50,000 female community health volunteers (FCHVs) are the CHWs in Nepal involved in community health programs for the last three decades. They serve as a link between government health services and local communities by imparting knowledge and awareness of health service availability, disease prevention, and health promotion [27, 28]. However, there is no evidence regarding the mobilization of FCHVs in the prevention and management of COPD in Nepal. There are important prospects of training and mobilizing FCHVs in curtailing the burgeoning burden of COPD in Nepal.

This article outlines the study protocol on the mobilization of FCHVs in public health activities to raise awareness for COPD prevention and its progression, called the Community-based intervention for prevention and management of COPD in Nepal (COBIN-P). This is a cluster randomized controlled trial (cRCT) aimed to evaluate the effect of a community-based home health educational intervention delivered by FCHVs on the prevention and management of COPD.

## Methods

This study protocol has been reported in accordance with the Standard Protocol Items: Recommendations for Clinical Interventional Trials (SPIRIT) guidelines (Additional file 1).

### Trial Design

A community-based, two-armed, open-label cluster-randomized controlled trial will be conducted in the semi-urban area of the Kaski district of western Nepal. It will be a parallel-group superiority trial with an allocation ratio of 1:1. The intervention time will be 12 months with assessments of outcomes at baseline and follow-up of the study.

### Study Settings

This study will be conducted in the semi-urban area of Pokhara (formerly known as Lekhnath Municipality). The study site is located in the Kaski district of western Nepal and is home to 58,816 residents, according to the 2011 census [10]. Similarly, 85% of the total population are literate, and the average life expectancy is 59.7 years [10]. It was administratively apportioned into 15 units called wards. The district public health office of Kaski district has reported 123 FCHVs working inside the municipality. Out of the ten health facilities, the Sisuwa Hospital is the only one with a provision of medical doctors, while the rest are run by a senior auxiliary health worker or health assistant. These facilities offer diagnosis and treatment for communicable diseases, including acute respiratory infection, diarrhea, tuberculosis, maternal and child health services comprising antenatal care, immunization, along with family planning and reproductive health services and non-communicable diseases services under Packages of Essential Non-communicable disease [29]. Our study will be an extension of a pre-existing Community-based Management of Non-communicable Diseases in Nepal (COBIN) project [30]. COBIN was initiated in 2013 and had thus far successfully concluded two studies on community-based management of hypertension and diabetes [31, 32]. No community-based interventions for COPD at the population level have been carried out in this study area to date.

### Study population

The study population is individuals aged 40 years and above in the municipality is 15,507 as per the latest census data. Firstly, the baseline information will be collected in all 15 wards. During the baseline survey, people living with COPD and participants at risk of COPD and a healthy population will be identified and recruited for the trial (Fig. 1).

**Fig 1 Fig1:**
[figure not shown]
Planned flow of participants through the trial. *FCHV* Female Community Health Volunteer

### Clusters

The 15 wards of the study area will constitute our clusters, but only 14 will be selected for the trial. We will randomly exclude one cluster by lottery method by an independent statistician. Allocation of the clusters into intervention and control arms is detailed in the section on randomization.

### Inclusion and exclusion criteria

Individuals aged 40 years and above who are listed in the voter list of 2007 as full-time residents of the study area are eligible for inclusion in the baseline survey. Those who can perform spirometry and provide the acceptable and reproducible spirometry graph to evaluate COPD will be included in the study intervention. Individuals, who are severely ill, who are unlikely to remain in the community throughout the intervention, who are pregnant women, who decline consent and have contraindications for conducting spirometry will be excluded from the study. The contradictions for spirometry include having active pulmonary tuberculosis or being on medications for pulmonary tuberculosis, thoracic, abdominal, or eye surgery in the last 6 months, history of mental illness, myocardial infarction in past 8 weeks prior to the study, and hospital admission in the past 6 months for cardiac illness [33].

### Sample size calculation

In the absence of a relevant Nepali study to take reference from for prevalence study, the sample size for this study is estimated according to the method suggested in the WHO STEPwise approach assuming the prevalence of COPD in Nepal to be 8% (a figure obtained from a Chinese study [34] and global burden of disease study based projection for Nepal [35]). When stratified by age group and sex (altogether eight groups in both sexes: 40–49, 50–59, 60–69, and ≥ 70), the sample size is 1508, when considering a 5% margin of error and expected response rate of 90%. Likewise, taking reference from a Chinese trial on community-based management of COPD for the expected mean difference between intervention and control arm as 19 ml FEV_1_ with a design effect of 1.83, considering an intracluster correlation of 0.01, the number of clusters per arm being 7, total sample size per arm will be 476 [36]. The coefficient of variation 0.45 was taken based on a previous study conducted in the same population [37]. Thus, the sample size required in the intervention for 80% of power and allowing 20% loss to follow-up will be 1143.

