### Randomization

The randomization approach, followed by the COBIN first trial on hypertension in Lekhnath Municipality, will be repeated in this study [30]. Out of 15 wards (clusters) in the municipality, one will be randomly excluded before randomization by lottery method. The remaining 14 clusters will be randomly assigned to the intervention and control group in 1:1 allocation ratio. The estimated sample size for the intervention study will be 1143. To include the study participants from every different sized clusters (wards), the required sample size of 1143 will be multiplied by the proportion of eligible participants in the ward. Then the intervention participants from each ward will be randomly selected. Research assistants will be blinded to the participants’ allocation status. To avoid selection bias following measures will be taken: (a) the randomization of the clusters will be done after the baseline survey, (b) clusters will not be withdrawn or added to the study, and (c) an independent epidemiologist will randomize the clusters.

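### The figure of 1143 adds 20% to 952 instead of dividing by 0.80, so it covers 16.7% loss to follow-up, not 20%; whether 80% power also allows for only 14 wards is not stated

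*Protocol article*

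**What the plan says.** Under Sample size calculation, the protocol article plans on an "expected mean difference between intervention and control arm as 19 ml" of FEV1, "with a design effect of 1.83, considering an intracluster correlation of 0.01". It continues with "an intracluster correlation of 0.01, the number of clusters per arm being 7, total sample size per arm will be 476". A coefficient of variation of 0.45 is also given, taken from earlier work in the same population. The paragraph closes by saying that "the sample size required in the intervention for 80% of power and allowing 20% loss to follow-up will be 1143".

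The same total is repeated elsewhere. The abstract has "The estimated sample size of the intervention will be 1143", Randomization has "The estimated sample size for the intervention study will be 1143", and Recruitment procedures again gives 1143 as the required size. The 80% power claim appears only under Sample size calculation.

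Three inputs are not printed: the standard deviation of the FEV1 outcome, the alpha of the trial, and whether 476 was obtained from normal or t quantiles. The only 5% in the paragraph belongs to the prevalence survey ("when considering a 5% margin of error and expected response rate of 90" percent).

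**The concern.** The number needed for analysis and the number to be recruited are linked by the loss rate, and both are printed, so a reader can check the step. It fails: the total equals the analysed number plus 20% of itself. Loss to follow-up is a fraction of those recruited, so the allowance has to be made by dividing by the retained fraction.

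The second matter is the small number of clusters. Seven wards per arm leave 14 - 2 = 12 between-cluster degrees of freedom for the treatment effect. A calculation that multiplies an individually randomised sample by a design effect, with normal quantiles, makes no allowance for this. The paragraph mentions none, though it does not rule one out.

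At stake is how a null result will be read. If 80% power is quoted for a design that gives somewhat less, a non-significant difference looks more informative than it is.

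**Working it through.** **Inputs from the protocol article:** 476 per arm; 1:1 allocation; 7 wards per arm; design effect (DE) 1.83; intracluster correlation 0.01; coefficient of variation 0.45, read here as that of ward size; 20% loss; 80% power; 19 ml difference. **Assumed:** two-sided alpha of 0.05.

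**1. The plan's own total**
- Analysed number: 2 x 476 = 952.
- 952 x 1.2 = 1142.4, rounded up to 1143. This reproduces the stated figure exactly.
- Correct allowance: 952 / (1 - 0.20) = 1190, which is 47 more (47 / 1143 = 4.1%).
- 20% loss from 1143: 1143 x 0.80 = 914.4, about 457 per arm and 38 short of 952.
- Loss that 1143 can absorb: 1 - 952 / 1143 = 16.7%.

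This step needs no standard deviation, no alpha and no outside source.

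**2. Power lost through this slip alone**

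Take the plan at its word that 476 per arm gives 80%. With normal quantiles, the expected test statistic at 476 per arm is 1.960 + 0.842 = 2.802. It scales with the square root of (n per arm / DE), and 476 / 1.83 = 260.1.
- DE held at 1.83, 457.2 per arm: 2.802 x sqrt(457.2 / 476) = 2.746; power 78.4%.
- DE recomputed for smaller wards: 1 + ((1 + 0.45^2) x 65.3 - 1) x 0.01 = 1.775. Then 2.802 x sqrt((457.2 / 1.775) / 260.1) = 2.788; power 79.6%.

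The second figure is slightly generous, because the same formula at 68 per ward gives 1.808, not the stated 1.83. Rescaling by 1.83 / 1.808 gives a DE of 1.797 and power of 79.1%. If 476 was instead obtained from t quantiles on 12 degrees of freedom, the same calculation gives 78.4% at DE 1.83 and 79.1% at DE 1.797. The slip therefore costs roughly 0.4 to 1.6 points.

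**3. Conditional check for few clusters**

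Suppose that 260.1 per arm came from normal quantiles and the test is on 12 degrees of freedom. Power from the noncentral t distribution is then:

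| Analysed | DE | Normal | t, 12 df |
|---|---|---|---|
| 952 | 1.83 | 80.0% | 73.0% |
| 914 | 1.83 | 78.4% | 71.3% |
| 914 | 1.797 | 79.1% | 72.1% |
| 914 | 1.775 | 79.6% | 72.6% |

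On this reading about 7 points come from the degrees of freedom and the rest from the inflation slip. Recruiting 1190 would restore 952 analysed but would still give 73.0%.

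**4. Standard deviation implied by 476**

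With normal quantiles the standardised difference is 2.802 x sqrt(2 / 260.1) = 0.2457, and 19 / 0.2457 is about 77 ml. With t quantiles on 12 degrees of freedom it is 0.2677, or about 71 ml. These values are solved back from the stated sample size. They are not figures the sponsor gives.

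**The case against.** A reader might infer that the trial simply has 71-73% power. The document does not support that as a flat statement. Dividing 476 by 1.83 always returns some number, and obtaining 260 does not show whether it came from normal or t quantiles. The paragraph names the seven clusters per arm among its inputs, so the cluster count was in view. The Analysis section specifies a mixed model ANOVA without saying how degrees of freedom are obtained. If 476 already allowed for 14 clusters, power with 914 analysed is just under 80%. This part of the objection stands, and the lower figures must remain conditional.

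It is also fair to say that the proven error is small: 47 people, about 4%, and under two points of power. Recruitment ended in September 2019, and the error changes neither the outcome definition nor the analysis nor the participants. That limits its severity.

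One could defend 1143 by reading the allowance as simply adding 20%. The sentence, however, allows for 20% loss to follow-up and claims 80% power after it, and 914 analysed is below the plan's own 952. The inflation error survives.

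**Conclusion.** The inflation error is established from the printed inputs alone: 1143 is 952 x 1.2, and 20% loss required 1190. The recruited number covers 16.7% loss. With a two-sided alpha of 0.05 assumed, the error by itself leaves power at about 78.4-79.6%.

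The few-clusters point is a separate and conditional one. It rests on three things that the article leaves open: the alpha, normal quantiles behind 476, and a test on 12 degrees of freedom. If all three hold, power is about 73% at 952 analysed and about 71-73% at 914. The range that the document supports is therefore from about 71% to just under 80%. Neither end should be presented as the trial's power until the sponsor states how 476 was derived.

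The point is of moderate severity: a wrong stated figure that is cheap to correct, with a modest certain effect and a larger possible one.

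**What to change.** - Keep 1143 as the recruited size in the abstract, Sample size calculation, Randomization and Recruitment procedures.
- In Sample size calculation, state that 1190 would have been needed for 20% loss, and that 1143 covers 16.7% loss, leaving about 914 analysed if 20% are lost.
- In the same place, state the standard deviation and alpha actually used, and whether 476 already allowed for seven clusters per arm.
- Restate the power for about 914 analysed from those inputs, using a reference distribution that reflects 14 clusters. On the article's figures and a two-sided alpha of 0.05, expect just under 80% if 476 already made that allowance and about 71-73% if it did not. The back-solved 77 ml or 71 ml should not be entered as the sponsor's assumption.

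The cost is a text correction and one recalculation. No extra enrolment is needed. The stated power will become slightly or moderately less favourable.

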### Survey tools

The survey tool includes information on socio-demographic information, behavioral information, and relevant questions on respiratory conditions. Spirometry will accompany the questionnaire survey. Data enumerators with minimum qualification of a bachelor’s degree in health sciences will be trained to measure lung function using diagnostic portable spirometers and conducting an interview using the survey questionnaire.

The questionnaire to be used in the baseline and follow-up will be adapted from the WHO STEPwise Surveillance tool and similar past studies that measured the burden of lung disease and its risk factors [34, 36, 38–42]. St. George’s respiratory questionnaire, which has been adapted and validated for use in Nepal, will also be used for COPD patients [43]. The socio-demographic information includes age, sex, education, occupation, and income. Lifestyle variables comprise detailed smoking history (current/former, type of tobacco use, intensity, and duration), environmental exposure to tobacco smoke at home or workplace, household fuel type use, and exposure to biomass fuel. Participants’ blood pressure, weight, and height will be measured, and body mass index calculated.

### Detection of airflow obstruction

The lung function measurement will be made using the diagnostic portable spirometer (ndd Medical Technologies EasyOne Air^TM^ Medizintechnik, Zurich, Switzerland) preferred for its accuracy, handiness, and calibration stability. Forced vital capacity (FVC) and forced expiratory volume in 1 second (FEV_1_) will be used as parameters to assess the degree of airflow obstruction and to make the diagnosis and severity of COPD. The airflow obstruction will be measured in terms of FEV_1_/FVC compared against the lower limit of normal (LLN) and GOLD criteria. This measure means that the ratio of FEV_1_/FVC below LLN or FEV_1_/FVC below 0.70 of predicted normal will be considered indicative of airflow obstruction. Population-specific reference equations are not yet available for Nepal, so reference values from the North Indian population will be taken [44].

American Thoracic Society (ATS) and European Respiratory Society (ERS) task force guidelines for spirometry will be adhered to, and the interviewers will be trained in following the guidelines [33]. Participants will be seated down upright in a chair and then asked to draw in as much air as possible and then hinted to release all the air as quickly as possible inside the spirometer mouthpiece for at least 6 s. A spirometry measurement will be considered to meet ERS/ATS criteria for acceptability and reproducibility, including having at least three attempts, two of which must be acceptable with a difference between the largest and second-largest values of < 150 ml for both FEV_1_ and FVC. The spirometer will be calibrated daily with a 3 L syringe, and each spirometry report will be printed and reviewed by a research investigator or physician, and if found unacceptable, the procedure will be repeated.

Those individuals demonstrating obstruction during the pre-bronchodilator test will be given a short-acting bronchodilator through an inhaler, followed by spirometry after 10 to 15 min. Those participants who demonstrate FEV_1_/FVC<LLN or FEV_1_/FVC< 0.70 of predicted normal during postbronchodilator spirometry will then be identified as COPD cases.

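### The obstruction and COPD case rules put the second cut-off at 0.70 of the predicted ratio, which makes the two-criterion rule LLN alone under the SDs assumed here; probably a wording error

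*Protocol article*

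**What the plan says.** All the operative text is in the protocol article, Methods, Detection of airflow obstruction.

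- **Standards named.** FEV1/FVC is to be "compared against the lower limit of normal (LLN) and GOLD criteria".
- **Obstruction rule.** "This measure means that the ratio of FEV_1_/FVC below LLN or FEV_1_/FVC below 0.70 of predicted normal will be considered indicative of airflow obstruction".
- **Who is retested.** "Those individuals demonstrating obstruction during the pre-bronchodilator test will be given a short-acting bronchodilator through an inhaler", with spirometry repeated 10 to 15 minutes later.
- **Case rule.** A COPD case is a person with "FEV_1_/FVC<LLN or FEV_1_/FVC< 0.70 of predicted normal during postbronchodilator spirometry".
- **Reference values.** Nepal has no equations of its own, so "reference values from the North Indian population will be taken". The article gives no predicted ratio, no SD and no percentile for LLN.

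No section of the article gives a plain FEV1/FVC cut-off of 0.70, and none gives GOLD's numerical criterion.

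**The concern.** An either/or rule built on two named standards should let each standard identify people whom the other misses. As worded, the second limb is a fraction of the predicted ratio and appears to fall so far below LLN that it can never act. A reader who follows the text applies LLN only. A reader who takes the phrase for a slip applies LLN or a raw ratio of 0.70. These rules can label different people as cases.

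Several things hang on the label:

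- who gets the post-bronchodilator test and is counted as a case;
- the prevalence result, since the abstract promises that "This study will estimate the burden of COPD";
- who completes the St. George's questionnaire, which "will also be used for COPD patients" (Survey tools), and so who contributes to a secondary outcome;
- the subgroups by COPD status and grade (Analysis);
- the parts of the package meant only for people with COPD: motivation for treatment, the status assessment guide and the breathing techniques (Study intervention).

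**Working it through.** The article states no figure to reproduce here, so the check compares the written cut-off with LLN.

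**Inputs.** From the article: the factor 0.70 applied to the predicted ratio, and the requirement of obstruction both before and after bronchodilator. Assumed, because the article gives none of them:

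- LLN is the 5th percentile, predicted − 1.645 × SD;
- predicted ratios run from 0.72 to 0.85;
- the SD of the ratio is 0.05 to 0.07;
- the ratio is normally distributed in the reference population.

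**Step 1: when can the literal limb act?** It needs 0.70 × predicted > predicted − 1.645 × SD, that is SD/predicted > 0.30/1.645 = 0.182. In ratio units the SD would have to exceed 0.30 × 0.72/1.645 = 0.131 at a predicted ratio of 0.72, and 0.30 × 0.85/1.645 = 0.155 at 0.85. The assumed SDs are 5.9% (0.05/0.85) to 9.7% (0.07/0.72) of predicted, well short of 18.2%. If LLN were the 2.5th percentile, the threshold would be 0.30/1.960 = 15.3%, and the conclusion would stand.

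**Step 2: where would a raw 0.70 act?** Wherever LLN is below 0.70, that is predicted < 0.70 + 1.645 × SD. This gives 0.782, 0.799 and 0.815 for SDs of 0.05, 0.06 and 0.07.

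**Step 3: how many does each version add to LLN?** For one test with cut-off c, the added share is max(0, Φ((c − predicted)/SD) − 0.05). Example: predicted 0.72, SD 0.07, c = 0.70 gives Φ(−0.286) − 0.05 = 0.388 − 0.05 = 0.338.

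For both tests, the added share is P(pre < c, post < c) − P(pre < LLN, post < LLN), with c the larger of LLN and 0.70. It uses a bivariate normal with assumed pre/post correlation 0.70 to 0.95 and an assumed mean post-bronchodilator rise of 0 to 0.03.

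| Predicted | 0.70 × predicted | LLN (SD 0.07 to 0.05) | Added, literal rule | Added, raw 0.70, one test (SD 0.05 / 0.06 / 0.07) | Added, raw 0.70, both tests |
|---|---|---|---|---|---|
| 0.72 | 0.504 | 0.605–0.638 | 0 | 0.295 / 0.319 / 0.338 | 0.120–0.302 |
| 0.75 | 0.525 | 0.635–0.668 | 0 | 0.109 / 0.152 / 0.188 | 0.031–0.161 |
| 0.78 | 0.546 | 0.665–0.698 | 0 | 0.005 / 0.041 / 0.077 | 0.001–0.063 |
| 0.80 | 0.560 | 0.685–0.718 | 0 | 0 / 0 / 0.027 | 0–0.021 |
| 0.82 | 0.574 | 0.705–0.738 | 0 | 0 / 0 / 0 | 0 |
| 0.85 | 0.595 | 0.735–0.768 | 0 | 0 / 0 / 0 | 0 |

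The literal limb adds nobody in any row. The single-test column is an upper bound for the raw rule, because the protocol requires obstruction on both tests.

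**The case against.** The strongest reply is that this is only a slip. The sentence that introduces the rule names GOLD as the second standard, and a reading that leaves that standard idle defeats the sentence it explains. Nothing in the article shows that anyone applied 70% of predicted in the field. That stands, and it is why the point is put as a probable wording error.

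Three further objections also stand in part.

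- The article never states GOLD's number, so it does not itself establish that a raw 0.70 was intended. The redundancy does not need that step: two standards are named, and as written only one does any work. But the fix has to begin by asking which rule was used.
- LLN, the SD and the predicted ratios are assumptions, and the shares in the table run from nil to a third. They describe a reference population at a fixed predicted ratio, not the participants. They show that the two readings are different rules; they do not measure harm done.
- The reach is limited. The primary comparison of FEV1 and FEV1/FVC and the sample size of 1143 do not use the label. One rule serves both arms and "the randomization of the clusters will be done after the baseline survey", so it cannot unbalance the arms at baseline. Home education goes to everyone in the intervention arm, and the tailored part also goes to those at risk.

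None of this removes the defect. The phrase stands in both operative sentences, nothing elsewhere corrects it, and someone following the text would apply a different case definition from someone reading past it.

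**Conclusion.** The point holds. Under a 5th-percentile LLN, and unless the reference SD exceeds 18.2% of the predicted ratio, the rule as written is LLN alone, although the protocol announces two criteria. A raw 0.70 would be a wider rule wherever the predicted ratio is below about 0.78 to 0.82.

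The practical size cannot be fixed from the article. On both tests, the difference under the stated assumptions ranges from none (predicted 0.82 and above) to 12–30% of a reference population (predicted 0.72). No number of reclassified participants is claimed.

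The threshold should be corrected because it sits in the case definition. It bears on prevalence, the quality-of-life population, the COPD subgroups and the COPD-only parts of the package, not on the primary result. Confidence is medium: the wording and the algebra are plain, but the SD is assumed and the rule applied in the field is unknown.

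**What to change.** First establish, and state, which cut-off was applied in the field.

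1. **If it was the raw ratio:** delete the words tying 0.70 to the predicted value in both sentences, so that the rule reads FEV1/FVC < LLN or FEV1/FVC < 0.70. Nothing else changes.
2. **If 70% of predicted was applied:** state that the working case definition was in effect LLN alone, and keep it for the packages delivered and the main COPD analyses. Then report prevalence and subgroup results under the raw 0.70 ratio, from stored spirometry, as a sensitivity analysis. Give the number of people who would be cases under that rule but lack a post-bronchodilator test or a questionnaire.

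The cost is a check of field records, then either one phrase removed twice or one clarifying sentence and one extra analysis. By the Trial status section, recruitment closed in September 2019 and endpoint assessment was due by the end of March 2021. Under option 2, missing baseline tests and questionnaires therefore cannot be recovered and the packages already delivered cannot be changed.
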